## Abstract

**Background:**

With rates of childhood obesity increasing, physical activity (PA) promotion especially in young children has assumed greater importance. Given the limited effectiveness of most interventions to date, new approaches are needed. The General Systems theory suggests that involving parents as intervention targets may be effective in fostering healthier life styles in children. We describe the development of a parent-focused participatory intervention and the procedures used to evaluate its effectiveness in increasing daily PA in preschoolers.

**Methods/Design:**

Thirty-seven South German preschools were identified for this study and agreed to participate. Using a two-armed, controlled cluster-randomized trial design we test a participatory intervention with parents as the primary target group and potential agents of behavioural change. Specifically, the intervention is designed to engage parents in the development, refinement and selection of project ideas to promote PA and in incorporating these ideas into daily routines within the preschool community, consisting of children, teachers and parents. Our study is embedded within an existing state-sponsored programme providing structured gym lessons to preschool children. Thus, child-based PA outcomes from the study arm with the parent-focused intervention and the state-sponsored programme are compared with those from the study arm with the state-sponsored programme alone. The evaluation entails baseline measurements of study outcomes as well as follow-up measurements at 6 and 12 months. Accelerometry measures PA intensity over a period of six days, with the mean over six days used as the primary outcome measure. Secondary outcomes include childrens' BMI, a sum of averaged skin fold thickness measurements across multiple sites, and PA behaviour. Longitudinal multilevel models are used to assess within-subject change and between-group differences in study outcomes, adjusted for covariates at the preschool and individual levels. Teacher qualitative interviews monitor the intervention implementation process.

**Discussion:**

Participatory approaches that actively involve parents have the potential to promote PA in ways that might be better tailored to local needs and more sustainable. Our mixed methods approach to assess the intervention efficacy and implementation employing both quantitative and qualitative measures within a cluster-randomized controlled trial may serve as a framework for evaluating public health interventions in preschool settings.

**Trial Registration:**

clinicaltrials.gov No: NCT00987532

## Background

Over the last 20 years, physical activity (PA) in children has decreased in both developed and developing nations [1]. Lack of PA is a key contributor to the epidemic of childhood obesity and a well-described risk factor for cardiovascular disease [1-4]. In addition to adverse metabolic effects, reduced childhood PA can negatively affect psychosocial factors such as self-esteem [5] and is associated with declining motor skills [6], which may, in turn, contribute further to inactivity. Effective interventions that address childhood PA are therefore urgently needed.

It is not known at what age PA promotion should be instituted to be most effective, but the preschool years may represent a window of opportunity. It is known that 'obesogenic' growth trajectories are often established during the adiposity rebound period [7]. Also, decreased levels of PA in elementary-school aged children are predictive of activity levels later in adulthood [8]. However, few randomized trials evaluating interventions in preschools exist and even fewer interventions have been shown to be effective in reducing overweight and inactivity [9].

Recent research, comprised primarily of studies targeting older children and adolescents, has identified several features that may influence intervention effectiveness [10]. For example, interventions of more than 6 months in duration and those that attempt to reduce inactivity rather than promote vigourous PA [9] may have greater effects. Moreover, efforts to create supportive environments (e.g. playground improvement) [11] and social support (peers, parents) [12-14] have been shown to yield positive results in promoting and sustaining behaviour change in general. Finally, evidence suggests that multi-component interventions may work better than single component interventions in changing health behaviours [15].

For PA interventions in preschool-aged children to be effective, the active involvement of parents may be particularly important. General Systems theory [16] supports this view by suggesting that the involvement of "social players" in a child's life provides role models and establishes patterns of normative behaviour that reinforce behaviour change in children. It is, however, not clear which methods for engaging parents in child PA promotion are most effective [17]. Based on experiences from community-based participatory research [18], a participatory approach including elements of choice, preference and co-determination might foster a sense of self-determination, create greater commitment and eventually lead to greater effects [19]. These features might also foster sustained behaviour changes - a major shortcoming of health promotion interventions that primarily rely upon educational and information-based strategies [20].

While parents were included in some standardized, educational interventions to promote PA in their children (e.g. through homework "assignments", or newsletters) [21-23], the effects of actively involving parents in determining intervention content and structure have not been studied. Their participation in interventions, however, might be essential especially because of their knowledge of the barriers to PA that their children face, but also because they have the best sense for opportunities for improvement that are consistent with their own and their child's preferences [24,25]. Furthermore, parental behaviour is one of the strongest determinants of both child physical activity [26] and Body Mass Index (BMI) [27], which means that involving parents within a participatory framework may foster more active lifestyles in the preschool years and beyond.

To test this hypothesis, we designed a parent-focused, multi-component, participatory intervention to promote childrens' physical activity in preschool settings. Here, we describe the development of the intervention and the methods currently being employed to assess its effectiveness by means of a cluster-randomized controlled trial.

### Theoretical Model

According to General Systems theory [16], health behaviours in children occur within an organic system of preexisting personal relationships and are influenced by a variety of factors including opportunities within the school environment, the home and the community, and the physical characteristics of these settings. Preschoolers' physical activity behaviour is influenced by the attitudes and behaviours of members of their larger network that includes parents, siblings, peer preschoolers and teachers. Although parents assume one of the most influential roles within this network in the preschool years, General Systems theory suggests that efforts to change behaviour should involve as many agents as possible, as behavioural norms develop as a consequence of interactions within the whole network [28].

The design of our parent-focused intervention "Ene mene fit - Eltern machen mit" (translated: Ene mene fit - parents join in) is based upon General Systems theory. The participatory intervention uses parents as the primary target group, but includes the entire preschool community (parents, teachers, children, peers) as potential agents of behavioural change. In order to actively involve the parents, the intervention uses strategies derived from community-based participatory research (CBPR) [18]. Our approach thus relies on the preschool network members' intimate knowledge about locally available resources and barriers to physical activity. This may help tailor the intervention to local needs and resources and may therefore yield greater success and sustainability.

## Methods/Design

### Setting and participants

The study is set in Baden-Württemberg, a federal state in southwest Germany. Its major goal is to increase physical activity in preschools, thus promoting the development of healthy behaviours in young children and decreasing their risk of overweight. With a population of nearly 11 million residents, Baden-Württemberg has an extensive network of more than 7,600 preschools located in urban, suburban, and rural settings, in which three to six year olds are enrolled and cared for by certified teachers. Most children attend preschool for five to seven hours daily.

Because no uniform national guidelines define a minimal frequency for physical activity lessons in preschools, significant variability exists in PA opportunities between preschools, ranging from curricular sport activities to unstructured play activities. To address this, a state-sponsored programme "Komm mit in das gesunde Boot" ("Come aboard the healthy boat") was initiated in 2006 to encourage physical activity among children in Baden-Württemberg. As part of this programme, specially trained external PA teachers deliver 40 standardized one-hour gym lessons over a six-month period (i.e. twice weekly) in preschools that participate in the programme.

The current study, "Ene mene fit", is a cluster-randomized trial embedded within the state-sponsored programme "Come aboard the healthy boat". It uses a two-level sampling strategy involving both preschools from three geographic regions that had formally applied for participation in the state-sponsored programme and the parents of children enrolled at these sites (see figure 1). Sites were excluded if they had less than 15 children participating in the state-sponsored programme or if there was no external PA teacher available in the area. Parents of any child enrolled at one of the recruited preschools in the intervention arm were potentially eligible for participation in the current parent-focused intervention.

**Figure 1 F1:**
[figure not shown]
**Study design**. Notes: n = number of preschools, N = number of children, SES = socioeconomic status.

### Intervention components

As a behaviour change strategy, "Ene mene fit" is best described as a complex intervention [29] in which specific components may vary across or within sites, even though each component serves a common purpose or function - to promote routine daily PA in preschool children. Following an extensive analysis of similar projects as well as a literature review, we first generated an initial pool of PA-promoting ideas for use by parents in the intervention arm using a number of techniques. Criteria for incorporating a project idea into the menu of options were that it 1) had already been implemented by parents or preschools in a German speaking community, 2) connected PA with activities of everyday life (e.g., the "walking bus" project for daily transport to preschool), 3) increased time spent outdoors [30] and 4) facilitated PA by building social networks between families. The latter criterion was based upon previous research describing parental lack of time as one of the major obstacles in increasing childrens' PA [25]. This lack of time might be overcome by sharing project responsibilities among several parents within a larger social network.

In a series of pilot tests, the initial pool of project ideas was further refined with input from parents of preschool-aged children. A convenience sample of 22 parents was invited to complete a questionnaire of both closed and open-ended items that assessed potential barriers and preferences for their childrens' PA and the support they might need to foster greater PA in their children. In a subsequent structured telephone interview, we also solicited opinions about the value and feasibility of the project ideas gathered so far as well as about new ideas on other kinds of projects. This process resulted in a menu of 15 easy-to-implement project ideas to promote everyday physical activity in children and families (table 1).

**Table 1 T1:** Excerpts of project idea menu

Evidence-based Principle	Project name	Project description
Active transport	„Walking bus“	Parents organize group walks to preschool (daily schedule)
	
	„Bicycle repair shop“	Parents meet on regular basis to repair bicycles and share skills with children or other parents. Location: either preschool or home garage

Lifestyle physical activity	„Preschool gardening“	Parents and teachers build a garden on the preschool's premises. Teachers involve children in gardening and growing plants.
	
	„Dances from all over the world“	Parents offer regular dance activities during the preschool hours.

Promotion of outdoor activities	„Campfire“	Parents organize regular weekend campfires together with groups of parents and children.
	
	„Forest trip“	Parents organize regular trips to the forest together with teachers during the week or on the weekend.

Reducing obesogenic traditions	„Birthdays and children's parties“	Parents and teachers organize "healthy birthdays" in preschool - Physical activity games and fruit and yoghurt instead of chocolate and cake

With the formal start of the intervention, project ideas were made available to parents on the study website http://www.ene-mene-fit.de and in a printed resource. To promote ease of use, we formatted the presentation of project ideas using four headings: 1) "Project Idea", 2) "Implementation Steps", 3) "Materials Needed", and 4) "More Details and Links". The primary goals in using this format were to provide sufficient details to enable implementation and to provide parents with a structured approach for adding their own project ideas to the website after the end of the formal intervention.

### Intervention structure

As part of the agenda at a regular convocation of parents and teachers, we introduced our intervention using a descriptive video. Following this, parents and teachers were encouraged to discuss barriers and resources for PA within their preschool and generate further ideas on how to enhance the physical activity of their families and among children in their local preschool. Subsequent steps over the course of three follow-up parent-teacher meetings consisted of 1) holding a workshop for project selection and establishing small project-specific teams, 2) team presentations to all parents as a way to motivate a greater number of parents, and 3) a workshop for planning the implementation. Interested parents and teachers were encouraged to identify up to four project ideas that could be taken either from the menu of project ideas or designed *de novo*. We encouraged new ideas, especially if they promoted PA connected to the childrens' everyday life, if they were inexpensive and relatively simple to implement and sustain. To help parents further, we made specially trained physical activity teachers available to offer support by helping to coordinate parent activities (e.g., by proposing time-lines), encourage participation and document the implementation of the project(s).

### Evaluation Design

Our study uses a cluster-randomized trial design, with natural preschool-bound clusters of children randomized to either the intervention or control arm. The evaluation strategy combines both quantitative and qualitative data collection and analyses. Quantitative outcome measurements will be obtained before the start of the intervention (baseline assessment), 6 months after baseline assessment (at the end of the state-sponsored gym lesson programme) and at 12 months after baseline assessment. Qualitative data collection, described in greater detail below, will allow for a closer examination of variation in the implementation process across and within intervention sites. In reporting our study, we will account for the recommendations of the CONSORT statement concerning complex cluster-randomized trials [31,32]. Baseline data from the completed recruitment to the study will be reported elsewhere.

### Recruitment and randomization

Of the 43 preschools applying for participation in the state-sponsored PA programme, we recruited 37 (86%) preschools and a total of 741 (78%) children (see figure 2). As previous research in children has shown differences in PA by physical setting [33] and in BMI by socioeconomic status [27], we stratified the randomization to balance preschool socioeconomic status (low, middle and high) and location (rural or non-rural) in both arms. Aggregate socioeconomic status (SES) of the preschool attendees was estimated by a tertile split based on information provided by the head teacher on the proportion of children from families with low SES or immigrant background. Because we hypothesized that a preschool's location (e.g., amount of green areas, big streets/highways and wooded areas) determined opportunities for PA, we developed a structured protocol to categorize preschools' setting as either rural or non-rural. Specifically, satellite views at a predefined altitude were examined independently by two research team members (Google Earth, accessed 6^th ^June 2008). Rural sites were defined as those that had forest, parks and green spaces within the cutout but no highways or industrial areas. All other preschools were categorized as located in a non-rural area. In each case, ratings were compared and differences were discussed until consensus was reached.

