**Figure 2 F2:**
[figure not shown]
**Evaluation design accounting for seasonal differences and using a waiting list control**. CONT = gym lessons (existing state-sponsored programme). INT = participatory parent-focused intervention plus simultaneous gym lessons. X1 and X2: randomization time points, X1 = autumn, X2 = spring. ---- children enrolled and measured, but no intervention/gym lessons.

Preschool assignment was blinded through the use of sequentially numbered, sealed envelopes. Preschools in the control arm (CONT) (n = 20; 371 children) receive the state-sponsored programme's gym lessons over six months as the sole intervention. Parents of children enrolled at preschools in the intervention arm (INT) (n = 17; 370 children) receive the participatory intervention, while their children also participate in the gym lessons. The participatory parent-focused intervention runs simultaneously with the gym lessons over the first six months, but continues for a total of at least nine months.

To account for seasonal differences in physical activity [34,35], the study was implemented at two time-points during the year: half of the preschools started the intervention in autumn 2008 with the other half starting in the spring 2009. To account for changes that occur as a consequence of physical maturation in children over time, the participatory intervention arm served as waiting list control during the first six months. Due to the participatory nature of the intervention, it was not possible to blind study participants or intervention providers. However, those involved in outcome assessment will be blinded to intervention assignment.

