### Assessment of intervention effectiveness

The intervention effectiveness is assessed by an intention-to-treat analysis.

Descriptive statistical analysis will be performed on all outcome measures. If needed, data will be transformed to better meet the assumptions of standard inferential statistical tests. We will use multilevel models to account for the structure of our data and for missing data on any of the measurements. In the multilevel model, repeated measurement of outcomes for each child will be considered the first "level"; these data are nested within preschools, which represent the second level. Differences between intervention and control group in primary and secondary outcomes will be analyzed in terms of fixed effects in the multilevel regression model, with age, sex, SES, immigration status and baseline BMI/accelerometer counts included as covariates on the individual level. In secondary analyses, the effect moderation by the preschool context as rated by qualitative data, as well as the level of implementation and adoption of the intervention will be analyzed.

Previous work documents a higher prevalence of overweight [63] and lower levels of physical activity [64] among immigrants. Because of the potential public health implications, we will conduct subgroup analyses at the child level comparing outcomes for normal-weight versus overweight children and for immigrant versus non-immigrant children. Subgroup analyses at the preschool level will be performed for rural versus non-rural locations and intervention timing (autumn versus spring) to assess the presence of potential effect modifiers.

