#### Sample size and power considerations

Previous published work provides little guidance on the extent to which PA-related outcomes in preschool children are inter-correlated. We therefore conservatively estimated the intraclass correlation coefficient (ICC) to be 0.1 ([65], personal communication concerning referenced trial). To detect a difference of 0.5 standard deviations (19.05 counts/15 seconds) between intervention and control group, assuming a standard deviation of 38.1 counts/15 seconds ([name], unpublished data from pilot studies in 4-5 year-old children) for accelerometry and an intraclass correlation of 0.1, with a power of 0.9 and alpha of 0.05 (two-sided), we estimated that a total of 504 children in 24 schools would be needed. We increased recruitment goals to 560 children (280 per arm) to account for a 10% loss to follow-up.

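### The preschool-level design factors (SES stratum, rural location, seasonal wave) are not named in the outcome model, and the abstract and the analysis section disagree on whether preschool-level covariates are adjusted for

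*Protocol article*

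**What the plan says.** Under Recruitment and randomization, the protocol article states: "we stratified the randomization to balance preschool socioeconomic status (low, middle and high) and location (rural or non-rural) in both arms". The reason given is prior evidence that activity varies with physical setting and BMI with socioeconomic status. The SES stratum is a tertile built from the head teacher's report of the share of families with low SES or an immigrant background.

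The trial also runs in two seasonal waves, introduced to deal with seasonal variation in activity: "half of the preschools started the intervention in autumn 2008 with the other half starting in the spring 2009". The Figure 2 legend adds "X1 and X2: randomization time points, X1 = autumn, X2 = spring".

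Under Assessment of intervention effectiveness, the arm difference is a fixed effect in a multilevel model, "with age, sex, SES, immigration status and baseline BMI/accelerometer counts included as covariates on the individual level". Location and timing appear in that section only as subgroup factors: "Subgroup analyses at the preschool level will be performed for rural versus non-rural locations and intervention timing (autumn versus spring"). Preschool context, implementation and adoption appear only as moderators in secondary analyses. The preschool SES stratum appears in no named analysis. The child's SES that is in the model is parental education (Covariates/confounders), which is a different variable.

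The Methods/Design part of the abstract describes the same models as "adjusted for covariates at the preschool and individual levels", without saying which preschool-level covariates are meant.

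**The concern.** The authors treat setting, preschool SES and season as prognostic: they stratified on the first two and staggered the starts because of the third. Balancing on a prognostic factor reduces the true variability of the arm contrast, but the analysis gains from this only if the factor is in the model. Otherwise its variance is counted as unexplained differences between preschools. That is where a trial of 37 clusters has the least information.

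Season matters most. Outcomes are measured at baseline, 6 and 12 months. A preschool that starts in autumn reaches its 6-month visit in spring, and one that starts in spring reaches it in autumn. A single visit effect common to both waves cannot describe that pattern. Adjusting for baseline counts does not remove it, because baseline and 6 months fall in opposite seasons in the two waves.

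The disagreement between the abstract and the analysis section also leaves open which preschool-level covariates enter the primary model, a choice that should be fixed before the outcomes are seen.

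**Working it through.** **1. The plan's own figure.** Inputs from Sample size and power considerations: difference 0.5 SD (19.05 counts with SD 38.1), ICC 0.1, power 0.9, two-sided alpha 0.05, 504 children in 24 schools (21 per school).
- Per arm without clustering: 2 × (3.2415 / 0.5)² = 84.06.
- Design effect: 1 + (21 − 1) × 0.1 = 3.
- Total: 84.06 × 3 × 2 = 504.4, against 504 stated. With 10% loss: 504 / 0.9 = 560, as stated.

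The sample size reproduces and is not in question.

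**2. Omitting wave, at the recruited number of preschools.** From the document: 20 control and 17 intervention preschools, 741 / 37 ≈ 20 children each, ICC 0.10, target 0.5 SD. Assumed: the two waves are of equal size and differ by s SD in mean counts at a visit, and the ICC of 0.10 does not already contain season.
- Variance of a preschool mean, in SD²: 0.10 + 0.90 / 20 = 0.145.
- An omitted two-level factor with difference s adds s² / 4.
- SE ratio = √((0.145 + s²/4) / 0.145).
- SE of the arm difference = √((0.145 + s²/4) × (1/20 + 1/17)).
- Power from the noncentral t with 20 + 17 − 2 = 35 degrees of freedom and noncentrality 0.5 / SE.

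| s (SD) | variance of preschool mean | SE (SD) | SE ratio | power at 0.5 SD |
|---|---|---|---|---|
| 0 (wave modelled) | 0.1450 | 0.1256 | 1.00 | 97% |
| 0.25 | 0.1606 | 0.1322 | 1.05 | 96% |
| 0.5 | 0.2075 | 0.1503 | 1.20 | 90% |
| 0.75 | 0.2856 | 0.1763 | 1.40 | 79% |

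These powers treat wave variation as ordinary random variation between preschools. If the arms are well balanced within each wave, the estimate itself does not vary with wave and only its reported SE is too large. Power is then roughly Φ((0.5 − 2.03 × SE) / 0.1256). At s = 0.5 this is Φ((0.5 − 0.305) / 0.1256) ≈ 94%, and at s = 0.75 it is Φ((0.5 − 0.358) / 0.1256) ≈ 87%. The table is therefore the pessimistic end for power; the SE inflation is the same either way.

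**3. Adding strata and wave, at the planned size.** Assumed: together they explain a share p of the between-preschool variance of 0.10. SE = √(2 × (0.10 × (1 − p) + 0.90/21) / 12).
- p = 0: 0.154 SD.
- p = 10%: 0.149 SD (4% smaller).
- p = 25%: 0.140 SD (9% smaller).
- p = 50%: 0.124 SD (19% smaller).

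The document gives neither p nor s, so both are shown as ranges.

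**The case against.** The strongest reply is that this is a condensed article. The covariate list in the analysis section is not declared exhaustive, and the abstract promises preschool-level adjustment. A reader might infer that the strata and wave have definitely been left out; the document does not establish that. What stands is narrower: a specific list confined to the individual level conflicts with the abstract, and the loss of precision follows only if that list is the whole model.

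A reader might also infer bias or a false-positive risk. Neither follows: leaving out balanced prognostic factors makes the standard error too large. A shift in the estimate from imbalance between waves is not supported either. The Figure 2 legend calls the two waves randomisation time points, which suggests allocation within each wave, and no arm-by-wave counts are given.

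Larger power losses can be produced by substituting a smaller effect. At 0.4 SD the same formula gives 87% falling to 84%, 74% and 60%, but the plan's target is 0.5 SD: "To detect a difference of 0.5 standard deviations (19.05 counts/15 seconds) between intervention and control group".

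Three further limits stand. The 0.75 SD case implies an ICC of (0.10 + 0.1406) / 1.1406 = 0.21, twice the value that the plan calls conservative. Child SES, immigrant status and baseline values absorb part of the preschool SES and location differences, and the working compares follow-up means without that adjustment. The opposite seasons are inferred from the 6-month spacing; Figure 2 is not available, and the waiting-list period leaves the visit timing partly unclear.

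**Conclusion.** The point holds as an inconsistency with a cost in precision. The abstract promises preschool-level covariates; the analysis section names none, although the trial was stratified by two preschool-level factors and randomised in two seasonal waves. If the analysis section is the complete specification, the standard error of the arm effect is inflated, by 5% to 40% over the assumed range of wave differences.

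Power at the planned effect stays at about 90% or more up to a wave difference of 0.5 SD, because 37 preschools were recruited against 24 planned. It drops to 79% only in the extreme 0.75 SD case, and by less if the arms are balanced within waves. The result rests on the assumed seasonal difference, an ICC that excludes season, and visit seasons inferred from the schedule. The consequence is a less sensitive test. The sample-size calculation is unaffected.

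**What to change.** Make the abstract and the section Assessment of intervention effectiveness agree by naming the preschool-level terms. State that the primary and secondary outcome models include, as fixed effects, preschool SES tertile, rural/non-rural location and randomisation wave, plus a wave-by-visit interaction, alongside the child-level covariates already listed. Keep the subgroup analyses by location and timing as separate, additional analyses.

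The data are already held and trial conduct does not change. The cost is four cluster-level degrees of freedom (two for SES tertile, one each for location and wave) plus the wave-by-visit terms. Going from 35 to 31 degrees of freedom leaves power at 0.5 SD at 97% (noncentral t, SE 0.1256), even if the added terms explained nothing. Fixing the terms before the outcome analysis also removes a later choice among preschool-level covariates.
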